##### Subgroup analyses

Subgroups will be analysed according to pre-defined design variables: over or under median age, shockable rhythm, sex, the presence of shock at admission, diagnosed AMI and over or under median time from arrest to ROSC. Difference in intervention effect estimates according to subgroup will be declared exclusively based on a statistically significant test of interaction.

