### Sample size estimation

The primary outcome is feasibility and the area under the NSE curve (NSE AUC) at 72 hours. Since no difference in feasibility is expected and the trial is designed as a pilot study, we have chosen to power this study according to differences in the NSE AUC. A difference of 20 % is defined as the minimal clinically relevant difference. Previous studies have found a value of approximately 20 μg/ml (25–75 % CI 10–45) at 72 hours [21]. We expect a mean AUC at 72 hours of 50 μg/ml*day, assuming an SD of 30 % of the mean AUC. The α is set at 0.025 (co-primary endpoint), which gives a power of 90 % if 50 patients are included in both groups. A 10 % loss of final measurement is expected (patients expiring before full 72 hours). Therefore, we aim to include 120 patients in total.

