### Statistical analysis plan

#### General principles

The general principles for statistical analyses will be:Analyses will be performed according to the intention-to-treat principle with patients lost to follow-up included in the denominator [22].A two-sided significance level of 0.025 will be applied to the primary endpoints and 0.05 will be applied to the secondary endpoints.The two trial sites will be asked to complete all CRFs and other forms if missing data is found in the electronic database. Missing data will be reported in the publication.More than 5 % missing data in outcome variables (see Endpoints) will result in multiple imputation with the creation of 10 imputed datasets to be analysed separately and then aggregated into one estimate of the intervention’s effect on the primary and secondary endpoints [23, 24].

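### A subgroup difference may be declared on any one of six uncorrected interaction tests, with no level, endpoint or exploratory label: about a 14 % (at 0.025) or 26 % (at 0.05) chance of a false declaration if the tests are independent

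*Protocol article*

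**What the plan says.** The Subgroup analyses section of the protocol article lists six factors, the last of them an interval that ends at ROSC: "over or under median age, shockable rhythm, sex, the presence of shock at admission, diagnosed AMI and over or under median time from arrest". They are fixed in advance: "Subgroups will be analysed according to pre-defined design variables". The decision rule follows: "Difference in intervention effect estimates according to subgroup will be declared exclusively based on a statistically significant test of interaction".

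The section does not say which outcome the interactions are tested on, at what level, whether the six tests are corrected for multiplicity, or whether the results are exploratory. The only significance levels in the article are under General principles: "A two-sided significance level of 0.025 will be applied to the primary endpoints and 0.05 will be applied to the secondary endpoints". Interaction tests are not mentioned there. Nothing elsewhere in the article limits the rule.

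**The concern.** The rule does two things. It forbids a subgroup claim that lacks a significant interaction test, which is good practice. It also makes one significant interaction test the whole basis for declaring a difference, and it applies this to six factors in turn. The first part guards against the error of finding significance in one stratum and not in the other. It does nothing about the chance that one of six tests is significant by luck.

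At stake is what the trial may conclude about who benefits. A false declaration would present a uniform effect as one confined to, or larger in, a group defined by age, rhythm, sex, shock, AMI or time to ROSC. The article says that it aims to minimise bias and data-driven reporting. A rule with an open level and an open endpoint works against that aim. The article also lowers the level to 0.025 because there are two co-primary endpoints (Sample size estimation), yet makes no comparable allowance for six declarable interactions.

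**Working it through.** The article states no subgroup error rate, so there is no figure to reproduce.

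**Inputs**
- Number of tests per outcome: k = 6 (Subgroup analyses).
- Level per test: not stated for interactions. The two levels in General principles, 0.025 and 0.05, are both used.
- Number of outcomes: not stated. One is assumed at first.
- Correlation between the tests: not given, so an assumption, shown as a range.
- True state: the same drug effect in every subgroup.

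**Independent tests.** The chance of at least one false declaration is 1 − (1 − α)^k.
- α = 0.025: 1 − 0.975^6 = 14.1 %
- α = 0.05: 1 − 0.95^6 = 26.5 %

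**Correlated test statistics.** For six normal statistics with common correlation ρ and two-sided critical value c, the chance is 1 − ∫ φ(u) [Φ((c − √ρ·u)/√(1−ρ)) − Φ((−c − √ρ·u)/√(1−ρ))]^6 du, with c = 2.241 for 0.025 and 1.960 for 0.05.

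| ρ | α = 0.025 | α = 0.05 |
|---|---|---|
| 0 | 14.1 % | 26.5 % |
| 0.3 | 13.0 % | 24.1 % |
| 0.5 | 11.3 % | 20.7 % |
| 0.7 | 9.0 % | 16.4 % |
| 0.8 | 7.5 % | 13.9 % |

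**Correlated patient factors.** A second check simulated 20,000 trials per setting with 120 patients ("Therefore, we aim to include 120 patients in total"), 1:1 allocation, a uniform effect and six binary factors. The factor prevalences (50, 80, 20, 20, 45 and 50 %) and a common latent correlation are assumptions. Each range covers runs with and without prognostic effects of the factors.

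| Latent correlation | α = 0.025 | α = 0.05 |
|---|---|---|
| 0.2–0.3 | 13.4–13.9 % | 25.2–25.8 % |
| 0.5 | 12.3–13.0 % | 23.0–24.1 % |
| 0.7 | 10.8–12.3 % | 20.4–22.4 % |
| 0.9 | 9.1–10.7 % | 17.5–19.8 % |

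Correlation between patient factors carries over only in part to the interaction tests, so these figures fall more slowly than those in the first table.

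**More than one outcome.** If NSE AUC is tested at 0.025 and one secondary endpoint at 0.05, and all twelve tests are independent, the chance is 1 − 0.975^6 × 0.95^6 = 36.9 %. Outcomes in the same patients are correlated, so this is an upper guide.

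**Power for a real interaction.** Sample size estimation gives a mean AUC of 50, an SD of 30 % of it (15) and a target difference of 20 % (10). Take a true interaction as large as that whole target effect, on the original scale and with a normal approximation.
- Median split, four cells of 30: SE = 15 × √(4/30) = 5.48 and 10/5.48 = 1.83. Power is 45 % at 0.05 and 34 % at 0.025.
- Assumed 80/20 split, cells of 48, 48, 12 and 12: SE = 15 × √(2/48 + 2/12) = 6.85 and 10/6.85 = 1.46. Power is 31 % at 0.05 and 22 % at 0.025.

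**With a correction.** At 0.05/6 = 0.0083 per test, the chance of a false declaration is 1 − (1 − 0.0083)^6 = 4.9 % if independent. At 0.025/6 = 0.0042 it is 2.5 %. Power in the median-split case falls to 21 % and 15 %.

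**The case against.** The quoted sentence is mainly a restriction. The factors are few, named and fixed in advance, an interaction test is required, and no primary or secondary conclusion rests on the result. Many statisticians would not ask for familywise control of six prespecified subgroups in a pilot. A condensed article may also leave detail to the full protocol or a separate analysis plan.

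Much of this stands. It limits the weight of the point and makes a multiplicity correction debatable as the main remedy. It does not remove the point. The article has its own section headed as the statistical analysis plan, and the difficulty lies in a rule stated there, not only in missing detail. Prespecification and interaction testing leave the 14 % or 26 % where it is.

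A reader might infer three stronger things that the article does not support.
- That the false-declaration rate is simply 21–26 %, or one trial in four or five. This needs 0.05 per test, which the article never assigns to interactions, and correlation no higher than moderate. If the subgroups concern NSE AUC, the article's own level is 0.025 and the rate is about 14 % or less.
- That a declared difference would probably be false. Power is low, but that conclusion also needs the prior probability of a real interaction, which is not given. The calculations support only the statement that such a declaration would be unreliable.
- That subgroup results will decide who enters the next trial. Nothing in the article says so.

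**Conclusion.** The concern holds in a limited form. The article lets a subgroup difference be declared on any one of six uncorrected tests and leaves level and endpoint open. For one outcome and a uniform effect, the chance of at least one false declaration is about 14 % at 0.025 per test and about 26 % at 0.05 if the tests are independent. It is roughly 8–13 % and 14–24 % for correlations of 0.3 to 0.8 between the tests, and higher if several endpoints are tested. Every figure is well above the per-test level. The choice of level, the correlation and the single outcome are assumptions, because the article fixes none of them. The primary analysis and its conclusion are untouched. The matter is worth correcting because it changes what the trial may claim and is easily put right.

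**What to change.** Amend the Subgroup analyses section, before unblinding, to say in substance: *Subgroup analyses are exploratory and are done on log2 NSE AUC. For each of the six factors the interaction estimate is reported with its 95 % confidence interval. A nominally significant interaction is hypothesis-generating and is not declared as a subgroup difference.* Keep the existing bar on subgroup claims made without an interaction test. The present section names no endpoint. NSE AUC is proposed because the trial is powered on it; if the sponsor prefers another endpoint, it should be named.

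If the sponsor wishes to keep the option to declare a difference, the section should require a Holm correction over the six factors at a stated family level. The first step is 0.025/6 = 0.0042 at the article's level for this endpoint, or 0.05/6 = 0.0083 if 0.05 is chosen and stated.

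The exploratory wording costs a few lines and no data. The Holm option sets a stricter bar for interactions that the trial has little power to detect in any case.

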### Ethical justification

Participation in the GLP-1 trial will not interfere with or delay routine diagnostic or therapeutic procedures. The trial investigates a potential beneficial effect of the GLP-1 analogue Exenatide, which seems to have effect in various degenerative neurological conditions and has been associated with reduced cerebral infarct size in animal studies. The current knowledge and safety data of intravenous infusion in patients with acute diseases have been referenced above.

The ethical justifications for interventions in the GLP-1 trial are as follows:Knowledge of the neuroprotective effect of GLP-1 analogues in comatose patients resuscitated after OHCA cannot be gained outside the acute setting. Research in a non-acute setting is not possible, and assessment in a human experimental model is obviously unethical.The interventions should be initiated as soon as possible after ROSC to alleviate the reperfusion injury and to reduce progressive brain injury by apoptosis. Therefore, consent from patients is not feasible and awaiting the consent of relatives would induce an unacceptable institutional delay of study drug administration in most cases.The administration of the study drug is considered safe and only exposes the patient to a minimal risk based on previous studies in patients with ST-elevation myocardial infarction [17].Increased knowledge of the therapeutic potential of pharmacological attenuation of anoxic brain damage would increase the scientific knowledge of the condition for the individual and other patients resuscitated from OHCA.Any relevant previously expressed objections to participation in clinical trials by eligible patients known to the researcher will be respected, including the termination of study participation by request from the next of kin.Inclusion in the trial may be of value to the individual patient but is valuable to the group of patients in general because further knowledge is needed to continue the optimisation of neuroprotective interventions in the post-resuscitation phase.

### Publication

The trial’s results will be published in international peer-reviewed journals with no restrictions. Authorship will be granted in accordance with the Vancouver Protocol. The physicians involved in the trial will write the resulting articles, and professional writers will not be used. The study database will be maintained for 15 years. [name] and [name] will be responsible for collecting the data for final analysis. The treatment allocation code will remain concealed until the database is locked. GCP monitoring is performed on the endpoints as well as on the inclusion and exclusion criteria. Analyses and data access will be logged and restricted hereafter. The dataset will be made publically available after 2 years by inquiry to the principal investigator (PI).

## Discussion

Due to the acute setting of this pharmaceutical trial in combination with the serious prognoses for the patients involved, a number of interesting challenges have arisen.

### Adverse events

Primarily, our population consists of severely ill patients with a high mortality rate. This makes adjudication of the AEs, SAEs and SUSARs challenging. Thus, the principal investigator or delegated investigator evaluates and adjudicates AEs on a day-to-day basis and reports to relevant authorities according to Danish legislation. In the event of a suspected SUSAR, the digital algorithm can unblind the treatment allocation of a single patient through the trial website. If this becomes necessary, it will be reported along with the results of the study.

### Surrogate endpoints

Secondly, our primary endpoint defined as area under the NSE-curve at 72 hours is a surrogate marker for poor neurological outcome and death. The surrogate marker is used instead of a hard endpoint in order to power this pilot study adequately. Previously, NSE has been shown to be a solid marker for poor outcome after OHCA in patients undergoing TTM, with an area under the receiver operating characteristics curve of 0.86 [26]. Thus, our surrogate endpoint reflects the clinically relevant question of whether Exenatide has neuroprotective effects in our population.

In conclusion, this article describes the design and planned analysis used in the GLP-1 trial for the first publication of the primary outcomes. This approach minimizes the overall risk of bias and data-driven results.

### Trial status

The trial is currently ongoing.

## Abbreviations

AE, adverse event; AUC, area under the curve; CPC, cerebral performance category; CPR, cardiopulmonary resuscitation; CRF, case report file; GCP, good clinical practice; GLP-1, glucagon-like-peptide 1; ICU, intensive care unit; MI, myocardial infarction; MRI, magnetic resonance imaging; mRS, modified Rankin scale; NSE, neuron-specific enolase; OHCA, out-of-hospital cardiac arrest; ROSC, return of spontaneous circulation; SAE, serious adverse event; SUSAR, suspected unexpected serious adverse reaction; TTM, targeted temperature management
